## Abstract

Long working hours can negatively affect workers' health, wellbeing, and work performance. Previous trials reducing working time have found improvements in multiple aspects of wellbeing, including sleep, job satisfaction, and reduced burnout, while maintaining performance. However, the potential psychological and biological mechanisms underlying these improvements, including immune function and brain function, remain unexplored. Therefore, the aim of this study is to understand the bidirectional relationship between working patterns and physical and mental health, and how workplace performance is affected. We aim to test at least 150 working-age adults in the UK (approximately half with a working time reduction and no loss of salary, and half controls with no change in working patterns) in a 14-week trial, including a 2-week baseline period, with additional participants completing questionnaires only. The primary outcome measure is the difference in physical and mental health from baseline to the end of the trial among participants undergoing a reduction in working time, compared with the control group. Data collection is currently underway, and while the majority of employers in the working time reduction group adopt a 4-day week format, the specific change in working patterns is flexible and varies between employers according to their operational need, including a 9-day fortnight, two half-days and shorter working days. Core variables include brain structure and function, sleep, immune function, interoception (perception of bodily sensations), time use, diet, mental health, and workplace performance and engagement. Secondary outcomes include weekly monitoring of self-reported wellbeing changes to identify key inflection points and assess whether these are maintained at a 6-month follow-up. Overall, this study aims to generate highly novel multimodal data on the psychological and biological implications of working time reduction, including observed changes in health, wellbeing, and performance.

## Introduction

1

Aspects of working life, including the amount of time spent at work, can negatively impact health and wellbeing (Afonso et al., 2017). In addition to affecting employees' quality of life, adverse health outcomes reduce performance and economic output by increasing the number of lost workdays (Bryan et al., 2021; Martinez et al., 2025). One approach to mitigate these harmful effects is to reduce working time. Under working time reduction models, employees' work time is reduced without a corresponding reduction in pay. In this way, working time reduction is distinct from part-time work, in which pay is reduced in proportion to working hours, and from compressed-hours contracts, whereby pay is maintained but the same working hours are compressed into fewer days rather than reduced. Under a 4-day week, for example, full-time employees typically transition from 5 to 4 days of work with no change in pay. The 4-day week has been described as a “100–80–100” working time reduction model, meaning that 100% of previous performance is undertaken in 80% of previous working hours, whilst retaining 100% of previous salary (Barnes and Jones, 2020). While the 4-day week is perhaps currently the most common form of working time reduction, other arrangements may be used, including a 9-day fortnight (one full workday reduced every other week), two half-days per week, or shorter days (Fan et al., 2025).

Landmark research on the effects of working time reduction has provided critical insight into the effects on employee wellbeing. Fan et al. (2025) present evidence from national cohort trials coordinated by the non-governmental organization 4 Day Week Global, drawing on data from the UK, Ireland, Australia, New Zealand, Canada, and the USA. Self-report data were collected from employees undergoing working time reduction (*n* = 2,896) and control employees experiencing no change in working time (*n* = 285). Following working time reduction, participants reported improvements in burnout and job satisfaction, suggesting benefits to employees' subjective experience of work. Additionally, participants reported improvements in both mental and physical health. These changes were not observed in control participants. Benefits were dose-dependent: greater individual reductions in working hours predicted greater improvements in wellbeing. Furthermore, improvements in wellbeing were mediated by reported changes in sleep problems, fatigue, and perceived work ability. Another working time reduction trial in Sweden also noted improvements in self-reported sleep quality and duration (Schiller et al., 2017). Indeed, self-reported improvements in wellbeing following the implementation of working time reduction are evident across multiple geographical contexts, including the UK (Lewis et al., 2023), Germany (Backman et al., 2026; Backmann et al., 2024), Portugal (Gomes and Fontinha, 2024), Iceland (Haraldsson and Kellam, 2021), Sweden and Norway (Lid Falkman et al., 2026). A recent scoping review of working time reduction trials reported consistent benefits to wellbeing, spanning physical health, mental health, and work-life balance (Utzet et al., 2026).

The findings from these working time reduction trials are supported by research exploring the relationship between length of working week, working patterns and aspects of health and wellbeing. Afonso et al. (2017) observed that participants working more than 48 h per week experienced greater symptoms of anxiety and depression, and poorer sleep quality, compared to those working fewer hours. Associations between longer working hours and sleep and mental health have also been noted in many other investigations (Nakashima et al., 2011; Ogawa et al., 2018; Ropponen et al., 2018; Virtanen et al., 2011, 2018; Virtanen and Kivimäki, 2012; Weston et al., 2019, although see for conflicting results: Varma et al., 2012). In addition, working 55 or more hours per week has been associated with less healthy diets and lower fruit intake (Baek et al., 2024). In a Korean all-female sample, Kwak et al. (2019) observed that shift workers had higher C-reactive protein levels, which are associated with poorer immune responses, than daytime workers. Longer working hours have also been associated with poorer physical health, with those working longer hours demonstrating a higher incidence of periodontitis, an advanced gum disease (Lee et al., 2021), and coronary heart disease and stroke (Kivimäki et al., 2015; Virtanen et al., 2012).

One might intuitively expect any reduction in working time to result in a proportional decline in performance. Performance refers generally to the observable quality of an individual's work. Within this, “productivity” is reflective of quantifiable outputs derived from one's performance, such the tasks achieved ([name] and Russell, 2025). Evidence in fact suggests that work performance is maintained, or sometimes even improved, when working time reduction models are applied. Across companies participating in the 2022 UK national trial, for instance, revenue remained stable, and staff turnover fell by 57% after implementing working time reduction (Lewis et al., 2023). At a more local level, a public sector trial in one English Council, found that of 24 key performance indicators (KPIs), 22 were maintained or improved, and staff turnover was reduced by 39% (Ainsworth, 2024). This was calculated to amount to a full year net cost saving of £371,500. Similarly, most business leaders participating in the Portuguese trial reported increased revenue relative to the previous year, alongside reductions in absenteeism and staff turnover (Gomes and Fontinha, 2024). The 2024 German working time reduction national trial showed no significant change (increase or decrease) in profit or revenue (Backmann et al., 2024), and performance was similarly found to be stable following a working time reduction trial conducted in Scotland's public sector (The Autonomy Institute, 2025). This maintenance of performance levels was attributed to work reorganization changes, including the implementation of “focus periods” for work, increased meeting efficiency, and the automation of common tasks.

The exact mechanisms by which reducing working time may benefit wellbeing without compromising performance remain unclear. However, observed benefits may be partly explained by the mitigation of detrimental health effects of long working hours. The Conservation of Resources (COR) theory (Hobfoll et al., 2018) suggests that workers are motivated to obtain and retain things they value. When resources that facilitate this (e.g., energy or time) are consistently stretched or depleted, an individual enters a protective state in which effective work is less likely, and the likelihood of burnout increases (Hobfoll, 1989; Hobfoll et al., 2018). The Job Demands-Resources (JD-R) model similarly considers the interplay between job demands, elements of work that require mental or physical effort, and job resources, factors that enable workers to achieve goals and personally develop (Bakker and Demerouti, 2007; Demerouti et al., 2001). When job demands exceed the resources available to deal with these, this can lead to job strain, which may undermine both health and work performance (Schaufeli et al., 2009). Meanwhile, Sonnentag et al. (2017) emphasize that resources depleted at work need to be restored through engagement in recovery processes, such as psychological detachment from work (Sonnentag and Fritz, 2015). Insufficient recovery experiences can impact wellbeing (Fritz et al., 2010; Sonnentag et al., 2010). Vandoros et al. (2025) highlight that transitions to reduced working time may empower employees to work more efficiently and adopt better time-management strategies, while health benefits stem from increased time allocated to recovery behaviors. [name] and Russell (2025) propose that observed benefits of working time reduction may operate through two complementary psychological mechanisms, with individuals being (a) better rested and (b) more motivated at work, both of which build resources to help manage job demands, and are facilitated by adaptive changes in brain function.

Indeed, emerging evidence links occupational stress to changes in brain structure and function. Neuroimaging studies have associated chronic work stress with cortical thinning of the frontal cortex (Blix et al., 2013; Savic, 2015), and localized enlargement of the amygdalae (Nasrullah et al., 2023), changes which have been associated with executive dysfunction (Yuan and Raz, 2014) and mental health conditions (Li et al., 2025), respectively. Conversely, Jang et al. (2025) observed that participants working more than 52 h per week had greater volume in frontal regions than those working fewer than 52 h. Functional disruptions have also been reported; participants experiencing greater occupational stress demonstrated altered prefrontal activity during verbal fluency tasks (Chou et al., 2016; Kawasaki et al., 2015), and reduced connectivity between the amygdala and both the dorsolateral prefrontal cortex and the anterior cingulate cortex, in conjunction with impaired emotion regulation (Golkar et al., 2014). A recent study using data from the UK Biobank found that participants working longer hours exhibited greater within-network connectivity in the somatomotor network (Souter et al., 2026). This association may reflect a maladaptive response in the context of highly demanding work, or an adaptive improvement to one's ability to work long hours; research using an intervention design would be required for further insight. To date, however, the effects of working time reduction on brain function using an intervention design have not been directly assessed.

Despite interesting wellbeing results from previous working time reduction trials, many share key methodological limitations. A review of working time reduction academic research by Campbell (2024) highlights the possibility of the Hawthorne effect (whereby participants' responses are influenced by their affinity for the research topic and motivation to report socially desirable outcomes), as well as a focus on self-report measures. Other limitations previously highlighted include a lack of data on individual compliance with working time reduction transitions, small and unrepresentative samples, and insufficient control groups (Cuello, 2023). Together, these limitations create opportunities for working time reduction study protocols that enhance scientific rigor and the potential to translate findings into policy change.

The project outlined below aims to build on the above findings, address identified limitations, and elucidate the mechanisms by which reducing working time simultaneously benefits performance and wellbeing. The “Sussex 4-Day Week” trial examines how working time reduction relates to outcomes across multiple health domains, including brain function (using functional magnetic resonance imaging), inflammatory cytokines (using blood serum samples), interoception (using heartbeat perception tasks), sleep (using actigraphy sleep watches and diaries), time use (using self-report diaries), and aspects of mental health and experience of work life (using self-report questionnaires). The inclusion of objective biomedical data addresses a key limitation of many historical trials, which often rely solely or primarily on self-report data. Additionally, this project aims to include a balanced control group not undergoing working time reduction to elucidate causal mechanisms underlying any observed effects. This protocol paper outlines the methodological framework for this investigation. To our knowledge, this is the first study to use a comprehensive multimodal protocol that integrates self-report measures, behavioral tasks with physiological monitoring, actigraphy sleep data, blood markers of inflammation, and functional neuroimaging to assess the effects of reduced working hours on the mind, brain, and body.

### Hypotheses

1.1

Across the multimodal protocol, we formulated hypotheses for each of our measures based on the existing literature and the proposed mechanistic pathways. These hypotheses specify the expected effects of working time reduction across the key behavioral, physiological, and neurobiological outcomes listed above.

#### Questionnaires

1.1.1

We record weekly measures of indicators of wellbeing, and performance to test how rapidly these change over time, informed by literature on recovery processes (Sonnentag and Fritz, 2015), COR theory (Hobfoll et al., 2018), and JD-R model (Bakker and Demerouti, 2007). We collected baseline and end-of-trial measures on additional occupational, wellbeing, and lifestyle measures commonly examined in workplace wellbeing research and that reflect longer-term resource changes as described in COR theory, JD-R model, and research on recovery processes (Bakker and Demerouti, 2007; Hobfoll, 1989; Sonnentag and Fritz, 2015). Based on these frameworks and previous findings from working time reduction research, we expect overall improvements in employee wellbeing and performance measures following working time reduction, compared to the control group.

#### Time-use diaries

1.1.2

To understand how time use changes with reduced working hours, participants can opt in to complete a time-use diary at the start and end of trial. Self-report paper time-use diaries have corresponded closely with objective measures of daily activities (Gershuny et al., 2020). Based on previous working time reduction studies, we expect employees in the 4-day week group to reallocate their time following the trial, with changes in activity categories such as travel time, household work, and free-time activities (Mullens et al., 2021; Schiller et al., 2018).

#### Sleep watch and diaries

1.1.3

Poor sleep is strongly associated with work-related stress and has significant consequences for workplace performance (Krause et al., 2017; Querstret and Cropley, 2012; Schiller et al., 2017; Wolkow et al., 2016; Yao and Basner, 2019). Sleep quality may be further compromised by work-related nighttime rumination, whereby employees continue to cognitively engage with work during non-work hours. In contrast, psychological detachment, the ability to mentally disengage from work during leisure time (Sonnentag and Fritz, 2007), is protective against these detrimental effects (Querstret and Cropley, 2012) and may be enhanced under a 4-day working week. Previous working time reduction studies, involving shorter daily working hours, suggest improvements in sleep quality and duration (Åkerstedt et al., 2001). However, these studies have not typically employed research-grade actigraphy (i.e., wearable sleep monitors) or examined finer-grained sleep metrics, and such objective sleep assessment has not yet been applied within a 4-day week trial. We expect improvements in sleep duration and quality during the trial for those undergoing a working time reduction. These effects may be enhanced by increased psychological detachment.

#### Blood sample

1.1.4

To evaluate immune function and inflammation, a blood sample is collected at the start and end of the trial to measure the serum concentrations of prototypical inflammatory markers, including C-reactive protein (CRP), and pro-inflammatory cytokines such as, interleukin-1 beta (IL-1β), interleukin 6 (IL-6), and tumor necrosis factor alpha (TNF). The serum concentrations of these molecules are known to be affected by stress, sleep, and poor mental health (De Azevedo Cardoso et al., 2023; Kennedy and Niedzwiedz, 2022; Reinhardt et al., 2016; Tang et al., 2025; Wolkow et al., 2015), but have not been investigated in relation to working time reduction. We expect a decrease in pro-inflammatory cytokine and CRP expression after a reduction in working time, likely in relation to improvements in other wellbeing markers, such as lower stress levels and improved sleep.

#### Interoception measures

1.1.5

Interoception is the sensing, interpretation and integration of signals originating from within the body by the nervous system, providing conscious and unconscious mapping of the body's internal systems on a moment-by-moment basis (Khalsa et al., 2018). Multi-dimensional models of interoception distinguish multiple dimensions of processing, including *interoceptive accuracy*—correct and precise monitoring of performance on objective behavioral tests of interoception; *self-report and interoceptive beliefs*—self-evaluated assessment of beliefs concerning interoceptive sensations and experiences accessible consciously and sub-consciously; and *interoceptive insight*—metacognitive awareness of experience and performance, e.g., confidence-accuracy correspondence (Suksasilp and Garfinkel, 2022). Furthermore, *trait interoceptive prediction error* assesses the discrepancy between objective accuracy and self-report interoceptive beliefs (Garfinkel et al., 2016). Greater positive prediction error (e.g., lower accuracy, higher self-report and interoceptive beliefs) is associated with anxiety (Garfinkel et al., 2016).

We expect an improvement in interoceptive accuracy following reduction in working hours, as reduced stress and better sleep are associated with enhanced interoceptive accuracy (Ewing et al., 2017). Furthermore, in clinical samples across various psychiatric diagnoses, lower accuracy is often accompanied by greater interoceptive beliefs than in control samples (Critchley et al., 2023; Garfinkel et al., 2016; [name] et al., 2019). Therefore, after working time reduction, lower stress and better mental health over a period of several weeks may be associated with a reduction in interoceptive beliefs, through less intense and/or less frequent self-perceived sensations, as assessed by self-report questionnaire (Body Perception Questionnaire above). Collectively, this may reduce trait interoceptive prediction error.

#### MRI scan

1.1.6

Multiple magnetic resonance imaging (MRI) sequences were chosen to investigate specific aspects of brain organization and function relevant to working time reduction. These include three functional MRI (fMRI) scans; two task-based scans investigating response inhibition and interoceptive focus; resting-state, diffusion-weighted imaging, and T1- and T2-weighted structural scans. Firstly, a stop signal task tests neural processes underlying response inhibition. This will measure changes in prefrontal function (e.g., Korucuoglu et al., 2021; Sharp et al., 2010). Second, an interoceptive focus task tests neural processes of interoceptive attention (Avery et al., 2015; Livermore et al., 2024)—the purposeful observation of internal bodily signals (Suksasilp and Garfinkel, 2022). This will measure changes in regions that process bodily stress signals, including the insular cortex (e.g., Craig, 2002; Schulz, 2016; Tan et al., 2018; Wiebking et al., 2015). Thirdly, resting-state fMRI will assess how signals within and across regions and networks covary with each other in the absence of explicit task instructions. From this, connectivity measures are extracted for regions and networks of interest. For example, connectivity in the default mode network is sensitive to stress (Clemens et al., 2017) as well as fatigue and depression (Høgestøl et al., 2019). Effects may also manifest as alterations in the differentiation of unimodal and multimodal regions, as measured using cortical gradients (Bernhardt et al., 2022; Margulies et al., 2016). Finally, diffusion-weighted MRI reflects white matter structure. Elements of lifestyle (sleep, diet, physical activity) are associated with white matter structure (Bruce et al., 2023; Li et al., 2020; Voldsbekk et al., 2021). As we expect lifestyle factors such as sleep, diet, and physical activity may change with working time reduction, it is possible such lifestyle changes are associated with changes to white matter.

## Methods and materials

2

### Participants and inclusion criteria

2.1

The study protocol was approved by the Brighton and Sussex Medical School Research Governance and Ethics Committee (RGEC; protocols ER/BSMS6337/4 and ER/BSMS6337/6) and conducted in accordance with the ethical standards set by the British Psychological Society and the Declaration of Helsinki. The study recruits two groups of participants: those undergoing working time reduction and control participants who do not change working hours.

We aim to recruit a balanced sample of at least 150 participants for all measures (with approximately half who reduce their working time and half controls). Sample size was determined using a power calculation in G^*^Power on questionnaire pilot data (*n* = 30) with an effect size of 0.45, alpha of 0.05 and power of 0.95. This suggests a group sample size of at least 68 is required. Furthermore, participation in certain study components is voluntary (e.g., MRI, blood sample, interoception, sleep, and time-use diaries), and therefore sample sizes are expected to vary across modalities as a consequence of participant self-selection and differential uptake of specific measures; accordingly, statistical power is also expected to vary between outcome domains. However, as this is the first working time reduction trial to use non-self-report measures, it was not possible to estimate power calculations beyond questionnaire data. In addition, as we will not examine moderating subgroup effects within the control group, fewer controls may be required. The primary purpose of the control group is to account for factors unrelated to the intervention itself, including practice effects, familiarity with the MRI scanning environment, and temporal changes that may occur irrespective of working time reduction. This will allow us to determine whether observed changes in outcomes can be attributed to the working time reduction intervention rather than repeated testing or assessment effects.

Participants in the working time reduction group are expected to achieve a “meaningful reduction” in average weekly working time, with original pay maintained (on par with inclusion criteria of recent national cohort trials, e.g., Fan et al., 2025). The majority of participants have switched to a 4-day week, with one full workday reduced each week. However, participants are not required to implement a 4-day schedule, and a minority have adopted other forms of work-time reduction, including a 9-day fortnight with one full workday reduced every other week, two half-days per week, or shorter days. This aligns with recent international cohort trials, in which the majority of participants switched to a 4-day week but were permitted to adopt other schedules according to organizational and individual preferences (Fan et al., 2025). For participants in this group, the research programme is explicitly referred to in recruitment materials as a “*4-day week study*.” Given the heterogeneity of work patterns adopted by employers across the trial, participants undergoing working time reduction will be referred to as the “working time reduction group” throughout this paper.

Control participants do not undergo any reduction in working time between the start and end of the research period. They maintain their original work schedule and pay. For participants in this group, the programme is referred to in recruitment materials as a “*workplace wellbeing study*.” No active deception is used; participants in this group are aware they are part of a larger study in which another group is receiving a reduction in working time.

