### Model design

3.2

This study uses a longitudinal mixed-effects design with a hierarchical structure. Repeated measures data are nested within employees, who are nested within companies, meaning observations are not independent and will be analyzed using multilevel methods. The design includes one between-subjects factor (group: intervention and control) and one within-subjects factor (time, which will vary per analysis with three datapoint options: baseline and end of trial; baseline, end of trial and 6-month follow-up; and the weekly questionnaires), with an interaction between time and group and corrections for multiple tests. When relevant, employee-level (e.g., age, household income) and company-level (e.g., industry, company size) covariates will be added to statistical models. Table 1 provides a list of all planned covariates. The independent variables will be fixed effects, with up to three random effects: time, employee, and organization. Covariates will be added to the model as fixed effects. This design enables us to determine whether changes are observed across time points for the working time reduction intervention group but not for controls.

**Table 1 T1:** Planned individual-level and company-level covariates for inclusion in statistical models.

Category	Covariate	Type
Individual-level	Baseline value of dependent variable	Continuous
	Gender or sex	Categorical
	Household income	Categorical
	Education level	Categorical
	Age	Continuous
	Living area	Continuous
	Job title	Categorical
	Hours of working time reduction	Continuous
	Remote work status	Categorical
Company-level	Industry	Categorical
	Company size	Categorical
	Trial start month	Categorical
	Profit status	Categorical

The specific coding scheme used for categorical variables alongside any data specific covariates will be specified in future modality-specific preregistrations.

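### The sample size uses one test at an uncorrected alpha of 0.05, while the model section announces multiplicity corrections for which the sizing makes no allowance

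*Protocol article*

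**What the plan says.** Section 2.1 (Participants and inclusion criteria) reports a G*Power calculation on questionnaire pilot data from 30 people, "with an effect size of 0.45, alpha of 0.05 and power of 0.95". It concludes: "This suggests a group sample size of at least 68 is required". The recruitment aim is stated as "We aim to recruit a balanced sample of at least 150 participants for all measures". The two groups are to be of roughly equal size, so about 75 per group. The section adds that "it was not possible to estimate power calculations beyond questionnaire data". It mentions no division of alpha.

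The Abstract defines the primary outcome broadly: "The primary outcome measure is the difference in physical and mental health from baseline to the end of the trial", compared with controls. The opening of section 3 widens the primary objective to health, wellbeing and work performance measures. Neither place names a single score.

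Section 3.2 (Model design) describes a multilevel model with group and time as factors, "with an interaction between time and group and corrections for multiple tests". It gives no family, method or number of tests. Section 3.3 calls an effect significant when p is below 0.05 and the 95% confidence interval excludes zero. It does not say whether either is adjusted.

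**The concern.** A power figure belongs to a particular test at a particular threshold. Section 2.1 uses 0.05 for one test. If the corrections in section 3.2 lower the threshold for an individual outcome, 0.95 at 68 per group no longer describes the chance of detecting an effect of 0.45 on that outcome.

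More than one test is likely. The wellbeing questionnaire alone (section 2.8.3) yields three DASS subscales, WHO wellbeing, the PSQI global score, IPAQ, diet quality and BMI, as well as the body perception score. The weekly and working-life scales come on top.

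At stake is how a result on a single scale is read. A non-significant corrected result could be given more weight as evidence of no effect than the design supports, because the only power figure in print is 0.95.

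**Working it through.** **Inputs from the document.** Effect size 0.45 (metric not named), alpha 0.05, power 0.95, 68 per group, and a target of about 75 per group.

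**Assumptions.** Two-sided tests; m tests in the family; Bonferroni threshold 0.05/m as the simplest case. The values of m are illustrative. The value m = 8 stands for the eight health scores listed above without the body perception score. No allowance is made for dropout or clustering.

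**Step 1: reproduce 68.** For a paired (within-group) t-test with standardized mean change d, the noncentrality is d√n on n − 1 degrees of freedom, and power is P(|T| > t(1 − α/2, n − 1)).
- At n = 68 the noncentrality is 0.45 × √68 = 3.71 and the critical value is 1.996. Power is 95.5%.
- The smallest n reaching 95% is 67, so this reading reproduces the printed figure to within one.
- A two-sample t-test with between-group d = 0.45 does not reproduce it. That needs 130 per group two-sided or 108 one-sided.
- Some ANOVA settings give 68, but only as a total. Examples are f = 0.45 for two balanced groups, and f = 0.225 for a group-by-time interaction with an assumed correlation of 0.5.

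**Step 2: lower the threshold under the paired reading.** For m = 8 the threshold is 0.05/8 = 0.00625 and the critical value at n = 68 rises to 2.823.

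| Tests (m) | Threshold | Power, n = 68 | Power, n = 75 | n for 95% |
|---|---|---|---|---|
| 1 | 0.05 | 95.5% | 97.0% | 67 |
| 2 | 0.025 | 91.9% | 94.4% | 78 |
| 3 | 0.0167 | 89.2% | 92.3% | 84 |
| 8 | 0.00625 | 80.9% | 85.6% | 99 |

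The margin between 68 and 75 does not absorb even a two-test correction, though it nearly does.

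**Step 3: less conservative methods.** This simulation used normal test statistics, 8 tests, correlation 0.3 to 0.5, n = 68 and 100,000 replicates. Uncorrected power on this scale is 96%. Average power for a truly affected outcome was:

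| Outcomes affected | Holm | Benjamini-Hochberg |
|---|---|---|
| 1 of 8 | 84% | 84% |
| 4 of 8 | 86% | 92% |
| 8 of 8 | 92–93% | 95–96% |

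The loss thus runs from about 12 points to almost nothing, depending on the method and on how many outcomes respond.

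**Step 4: the between-group reading.** If 0.45 were a between-group d, power at 68 per group would be 74.1% before any correction. At 75 per group it would be 78.2%, falling to 63.1% for 3 tests and 49.5% for 8. This matters for the wording of the fix.

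**Step 5: set section 3.3 beside section 3.2.** If p in section 3.3 is unadjusted, it matches the alpha in section 2.1 but conflicts with the corrections in section 3.2. If p is adjusted, it fits section 3.2 but not the alpha in section 2.1, and an ordinary 95% interval is not the interval that matches an adjusted p-value.

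**The case against.** The strongest reply is that the corrected criterion is not in this document. The phrase in section 3.2 follows a list of time structures, so it could mean correction across time contrasts or within one data type. Section 3 defers data-type detail to preregistrations, and leaving the family and method to them is normal for an article. That stands: the absence of a family or method is not the fault here. What remains is that a stated power and a stated intention to correct appear together without being connected. A preregistration can choose the method, but it cannot make a single-test power apply to a lower threshold.

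A second reply is that questionnaire numbers may exceed 68. The Abstract adds questionnaire-only participants, and section 2.2 offers questionnaires to all staff. This also stands. Under the paired reading, 99 per group would restore 95% for eight Bonferroni tests. The document gives no planned questionnaire number, so the gain cannot be credited.

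Third, section 1.1.1 expects broad improvement, which is where Holm and FDR methods lose least. That is fair, and it limits the size of the point.

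A reader might go further and infer that 68 is an arithmetic error, or that power is a definite 10 to 15 points below what is claimed. Neither is supported. The figure reproduces at an undivided alpha, and any fixed loss depends on an assumed family. Nor does the article describe the whole study as 95% powered: section 2.1 says power will vary between outcome domains. It attributes that variation to voluntary uptake, however, and does not mention multiplicity.

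**Conclusion.** The point holds as a mismatch that needs reconciling. The sizing in section 2.1 is for one questionnaire test at an uncorrected 0.05. Section 3.2 announces corrections, the primary outcome spans several scales, and section 3.3 leaves it open whether p is adjusted.

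The size is illustrative only. Under a two-sided paired test with effect 0.45 and Bonferroni correction for 2 to 8 tests, power is 92% to 81% at n = 68 and 94% to 86% at n = 75. It is close to the single-test value if all or nearly all outcomes respond and FDR control is used. Under Holm with half the outcomes affected, the loss is still about 10 points at n = 68.

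These figures rest on the assumed family, the assumed method and the paired reading of 0.45. The paired reading is itself a within-group pre-post test, whereas the stated objective is a comparison with controls, so 0.95 should not be taken as established for that comparison.

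**What to change.** In section 2.1, state that the calculation is for one uncorrected questionnaire test, and name the test and the effect metric behind 0.45. Then take one of two routes:

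1. Restate the power at the planned questionnaire sample size under the correction that section 3.2 will apply, giving the family and method.
2. Name one primary questionnaire score to be tested at 0.05, limit the sizing claim to that score, and apply the correction to the remaining outcomes.

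In section 3.3, say whether p < 0.05 refers to adjusted p-values and make the confidence interval rule consistent with that. Do not reprint 0.95 as valid for the between-group comparison without first checking it against the named test and metric.

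The cost is a few sentences here and in the questionnaire preregistration. No extra recruitment is needed. The downside is a less favourable stated power.
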